## Abstract

**Background:**

Patients with chronic kidney disease (CKD) are at a greatly increased risk of developing cardiovascular disease. Recently developed guidelines address multiple risk factors and life-style interventions. However, in current practice few patients reach their targets.

A multifactorial approach with the aid of nurse practitioners was effective in achieving treatment goals and reducing vascular events in patients with diabetes mellitus and in patients with heart failure. We propose that this also holds for the CKD population.

**Design:**

MASTERPLAN is a multicenter randomized controlled clinical trial designed to evaluate whether a multifactorial approach with the aid of nurse-practicioners reduces cardiovascular risk in patients with CKD. Approximately 800 patients with a creatinine clearance (estimated by Cockcroft-Gault) between 20 to 70 ml/min, will be included. To all patients the same set of guidelines will be applied and specific cardioprotective medication will be prescribed. In the intervention group the nurse practitioner will provide lifestyle advice and actively address treatment goals. Follow-up will be five years. Primary endpoint is the composite of myocardial infarction, stroke and cardiovascular mortality. Secondary endpoints are cardiovascular morbidity, overall mortality, decline of renal function, change in markers of vascular damage and change in quality of life. Enrollment has started in April 2004 and the study is on track with 700 patients included on October 15th, 2005. This article describes the design of the MASTERPLAN study.

## Background

Patients with chronic kidney disease are at a greatly increased risk of developing cardiovascular disease (CVD)[1,2]. This is most prominent in patients on renal replacement therapy but also firmly established in patients with mild renal dysfunction[3]. This increased cardiovascular risk in patients with chronic kidney disease (CKD) is the resultant of a multitude of risk factors. Among these risk factors are: all known traditional risk factors, a number of them evidently more prevalent than in the general population, risk factors that are associated with or worsened by renal insufficiency (anaemia, disturbances in calcium-phosphorusbalance, oxidative stress, inflammation) and renal insufficiency itself [4-7].

Several guidelines have been formulated, both nationally and internationally, to assist physicians in adequately reducing cardiovascular risk [8-11]. However it is well known that patients do not reach treatment-goals formulated in these guidelines[12]. This has also been established in patients with renal disease[13,14]. In patients with diabetes mellitus and heart failure a multifactorial intervention implemented by nurse-practitioners significantly improved metabolic control and reduced cardiovascular events [15-18].

Given the high cardiovascular risk and the multitude of modifiable risk factors a multifactorial approach could very well also be of benefit for patients with CKD. This has been suggested several times but has never been proven. [4,19,20] Most risk factors that promote CVD also promote decline of renal function. Effectively addressing these risk factors might therefore also delay renal function decline[21,22].

## Design

The MASTERPLAN study is designed as a multicenter randomized controlled clinical trial with a duration of 5 years of follow-up.

### Aims & primary outcome

The MASTERPLAN study aims to show that in patients with mild to moderate CKD strict implementation of current guidelines by a nurse practitioner, with emphasis on the use of cardioprotective medication and lifestyle changes, results in a reduction of a composite endpoint of myocardial infarction, stroke and cardiovascular mortality.

Cardiovascular morbidity, overall mortality, quality of life, percentage of patients achieving treatment goals, changes in renal function and changes in markers of vascular damage will be considered as secondary outcomes.

### Measurements

Changes in renal function will be documented by annually measuring creatinine clearance from a 24-hour urine sample and measurement of the serum creatinine. Quality of life will be assessed through questionnaires that will be filled out by all participants annually. Markers of vascular damage will be recorded annually in a proportion of the patients. These markers address different aspects like endothelial function, arterial compliance and atherosclerosis in various vascular beds. Pulse wave analysis (PWA) and pulse wave velocity (PWV) will be measured in approximately 300 patients. Aortic pulse wave forms and aortic pulse wave velocity are indicators of arterial stiffness. PWV has been shown to be an independent predictor for cardiovascular risk[23,24]. PWA and PWV measurements have been validated and can be measured in a reproducible manner[25]. Carotid intima media thickness (CIMT) evaluation through B-mode sonography will also be measured in approximately 150 patients. Increased CIMT is associated with an elevated risk of cardiovascular disease[24]. Change in CIMT has been shown to result from risk factor modifications in a variety of populations[26]. CIMT measurement has been validated and shown to be reproducible[27].

Blood pressure will be recorded twice per year using a non-invasive automated oscillometric device. Patients will stay in a supine position for 30 minutes, blood pressure will be recorded every three minutes. The last five measurements will be used for analysis. Conventional office readings using the auscullatory method will also be documented.

### Recruitment and screening

All subjects will be recruited from the outpatient nephrology or internal medicine clinic of nine Dutch hospitals. Patients are identified by checking their medical records for compatibility with the inclusion criteria prior to a regular outpatient visit. Renal function will be estimated using the Cockcroft-Gault formula (with a correction for body surface area as of April 15^th ^2005)(appendix A). The Cockcroft-Gault equation has been extensively validated and is generally appreciated as a useful tool to estimate creatinine clearance[28,29]. The physician will give every eligible patient a brief verbal explanation and extensive written information about the study. A week later follow-up by the nurse practitioner will be performed. Upon verbal consent to participate in the study, the patient will be invited to the office. In this visit the in- and exclusion criteria will be checked thoroughly, written informed consent will be acquired and subsequently baseline measurements will be performed. The medical ethics committees of the participating hospitals have approved the conduct of the study.

Recruitment began in April 2004 and is estimated to continue until December 2005. About 60% of patients deemed eligible by their physician and asked to participate in the study, actually participate and are included. The main reasons for non-participation appear to be: reluctance of the patient to changes in drug therapy and inability of the patient to attend the required visits. On December15, 2005 793 patients had been included.

### In- and exclusion criteria

Patients are eligible for inclusion when they fulfill the following criteria:

• The subject is at least 18 years old

• The subject is diagnosed with CKD with a creatinine clearance estimated by the Cockcroft-Gault equation between 20 and 70 ml/min.

• The subject is able and willing to provide written informed consent

The following conditions are considered exclusion criteria:

• A renal transplant less than a year before inclusion

• Acute renal failure or rapidly progressive glomerulonephritis established by the treating physician

• Any malignancy less than five years before inclusion other than basocellular or squamous cell carcinoma of the skin.

• Participation in other clinical trials requiring the use of study medication

From April 15^th ^2005 until the end of the inclusion the Cockcroft-Gault equation was modified to take into account body surface area according to recent insights into the applicability of formulas to estimate renal function [30-33]. This modification was approved by the medical ethics committee.

### Baseline evaluation and randomization

Table 1 summarizes the data collected at baseline evaluation. After the baseline evaluation, the patient will be randomized to either nurse practitioner care or physician care. Randomization to treatment is stratified by center and renal transplant status using a web-based randomization module and performed in predefined blocks of certain numbers of patients.

**Table 1 T1:** Data collection

Visit	Baseline 1	Visit 2	Visit 3	Visit 4	Visit 5
Month	0	3	6	9	12

Informed Consent	x				
Demographic data	x				
Medical history	x				
In- and exclusion criteria	x				
Randomization	x				
Endpoints		x	x	x	x
Weight	x	x	x	x	x
Waist-hip ratio	x				x
Ankle-Brachial Index	x				x
RR and HR in sitting position	x	x	x	x	x
RR 30 minutes Dynamap	x		x		x
Smoking habit	x	x	x	x	x
Medication use	x	x	x	x	x
Three monthly Laboratory evaluation^a^	x	x	x	x	x
Annual Laboratory evaluation ^b^	x				x
ECG	x				x
PWV (Proportion of patients)	x				x
Carotid-IMT (Proportion of patients)	x				x
Questionnaires ^c^	x				x

a: Three monthly Laboratory evaluation: Hematology: Hb, Ht, trombocyte count; Chemistry: sodium, potassium, calcium, phosphate, bicarbonate, urea, creatinine, albumin; Urinalysis: spot urine creatinine, albumin, total protein

b: Annual Laboratory evaluation: Hba1c, uric acid, PTH, total-cholesterol, HDL-cholesterol, LDL-cholesterol, triglycerides; Urinalysis: 24 hr urine sodium, creatinine, albumin, total protein

c: Questionnaires: Quality of Life: SF-36, EQ-5D; Physical activity: SQUASH; Dietary composition; Erectile dysfunction

### Treatment groups

To all patients the same set of guidelines and treatment goals, represented in Table 2 and Table 3, apply. Both patients and physicians are provided with information about the beneficial effects of multifactorial risk factor management regardless of treatment allocation. In the intervention group nurse practitioners, supervised by a qualified nephrologist, will actively pursue lifestyle intervention (physical exercise, nutritional counseling, weight reduction and smoking cessation), the use of specified cardioprotective medication and the implementation of current guidelines. The nurse practitioner will check regularly whether treatment goals have been met and when deemed appropriate adjust treatment to achieve target values. Modification of therapy will be executed according to flowcharts that have been derived from current guidelines.

**Table 2 T2:** Goals and relevant guidelines for cardiovascular risk factors in MASTERPLAN

Risk factors	Goal	Guideline
Blood pressure	</= 130/85 mm Hg^a^	NFN^b^8, KDOQI^c^[10]
Proteinuria Protein excretion in urine	< 0.5 g/day	KDOQI^c^[10]
Lipids		KDOQI^c^[11,44]
Fasting LDL	< 2.6 mmol/l	
Anemia		NFN^b^[45],
Hemoglobin concentration	> 6.8 mmol/l	KDOQI^c^[46]
Glucose		NHG^d ^[47]
Fasting glucose	< 7.0 mmol/l	
Non Fasting glucose	< 9.0 mmol/l	
Calcium and Phosphate metabolism		NFN^b^[8],
Phosphate	</= 1.8 mmol/l	KDOQI^c^[48]
PTH	< 18 pMol/l**	
Healthy Nutrition		GR^f^[49]
Protein	0.8–1.0 g/kg ideal bodyweight/day	
Sodium	2000 mg/day	
Fat	Reduce fat, unsaturated fats preferred	
Energy	30–35 kcal/kg ideal bodyweight/day	
Overweight Body mass Index	<25 kg/m^2^	
Physical exercise	5×/week 30 minutes moderate exercise	NNGB^g^[50]
Smoking	To Quit	NFN^b^[8]

a In case of proteinuria > 1 g/day: 125/75 mm Hg

b NFN: Nederlandse Federatie voor Nefrologie (Dutch Federation for Nephrology)

c KDOQI: Kidney Disease Outcomes Quality Initiative

d NHG: Nederlands huisartsen genootschap (Dutch College of General Practitioners)

e smaller than three times the upper limit of the normal range f GR: Gezondheidsraad (Health Council of the Netherlands)

g NNGB: Nederlandse Norm voor Gezond Bewegen (Dutch Standard of Healthful Physical Activity)

**Table 3 T3:** Standard medication to reduce cardiovascular risk in MASTERPLAN

Medication	Recommended dose	Point of impact
HMG-CoA Reductase Inhibitor (statin)	e.g. atorvastatin 10 mg daily (or comparable dose of other statin)	Lipid-metabolism
Acetylsalicylic acid	80 mg daily	Thrombocyte aggregation
Folic Acid	5 mg daily	Homocysteine metabolism
ACE inhibitor or Angiotensin Receptor Blocker (ARB)	e.g. enalapril 5 mg twice daily (or comparable dose of other ACE inhibitor) or irbesartan 75–150 mg (or comparable dose of other ARB) daily	Blood pressure, renal function and cardiac pre- and afterload

a In case of proteinuria > 1 g/day: 125/75 mm Hg b NFN: Nederlandse Federatie voor Nefrologie (Dutch Federation for Nephrology) c KDOQI: Kidney Disease Outcomes Quality Initiative d NHG: Nederlands huisartsen genootschap (Dutch College of General Practitioners) e smaller than three times the upper limit of the normal range f GR: Gezondheidsraad (Health Council of the Netherlands) g NNGB: Nederlandse Norm voor Gezond Bewegen (Dutch Standard of Healthful Physical Activity)

Physician care comprises 'usual care' conform the guidelines mentioned in Table 2. In contrast to the intervention group and in agreement with real life practice no extra incentives to adhere to the guidelines will be supplied.

### Clinical data

The intervention group will receive follow up by the nurse practitioner as often as is indicated by the guidelines and the sort of lifestyle intervention the patient receives. Additional data will be collected for trial purposes quarterly as described in table 1. The physician care group will receive an automated non-invasive blood pressure measurement two times a year. Annually each patient will be invited in the office to undergo a series of measurements and to fill out questionnaires. At the other time-points (represented in Table 1) present clinical data derived from the medical records will be recorded in the case report form.

The patients will fill out several questionnaires. Firstly quality of life will be assessed using the SF-36 (Dutch version) and EQ-5 D (Dutch version) questionnaires[34,35]. Secondly the Short Questionnaire to asses health enhancing physical activity will be given to subjects[36]. Thirdly a Food questionnaire developed by the Wageningen University will deliver information about the composition of the diet of the subjects[37].

### Data management

The entire study is performed according to the ICH-GCP guidelines, including on-site monitoring. The data will be documented in a case report form, via a validated web-based structure. Investigators will fill out the required data of a visit in an Internet application based on PDF files. Upon completing the form they will start the submission process. Before submission the data are verified and passed through an editing process to check for logical inconsistencies within the data. Any discrepancies need to be corrected before actual submission can take place. The data will be sent to a web server located in the data management center. The data are immediately transferred into a SQL server database.

The questionnaires are all in Teleform format and mailed to the data management center. Filled out questionnaires are scanned and data are immediately transferred to the same database used to store the clinical data. A specified validation procedure has been developed to check inconsistencies and to generate and process queries.

### Endpoint collection and evaluation

The primary endpoint has been defined as follows, based on experience in other studies run at the UMCU [38,39].

• Myocardial infarction is defined as evident new ischemic changes on an ECG or an established rise and fall pattern of cardiac enzymes.

• Stroke is defined as characteristic clinical symptoms of stroke accompanied by signs of recent ischemia using an appropriate imaging technique (CT-scan or MRI).

• Cardiovascular mortality is defined as death due to myocardial infarction, stroke, ruptured abdominal aneurysm, and terminal heart failure. Also sudden death will be regarded as part of cardiovascular mortality.

All suspected events, which might contribute to the primary endpoint, will be evaluated by an independent endpoint-committee. The committee will evaluate these events using definitions for the different events which are also used in other Dutch trials [38,39].

Secondary endpoints are collected via clinical data, questionnaires or specified procedures. The SphygmoCor system (pulse wave velocity system and blood pressure analysis system, PWV Inc., Sydney Australia) is used to assess PWV and to analyze the arterial pulse contours. Pulse contours will be obtained by applanation tonometry at the carotid, radial and femoral arteries. Independent investigators blinded for treatment allocation of the subject will perform evaluation of recorded data. CIMT assessment will be performed using B-mode ultrasonography of both carotid arteries with a 7,5-MHz linear array transducer to assess the presence of plaques in the common carotid artery, bifurcation and internal carotid artery. All measurements will be recorded on video and evaluated off-line by independent evaluators blinded for treatment allocation of the patient [40].

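### The primary composite is said to include stroke, but the only definition counts imaged ischemia alone, so non-fatal haemorrhagic strokes are left out

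*Protocol article*

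**What the plan says.** The abstract states: "Primary endpoint is the composite of myocardial infarction, stroke and cardiovascular mortality". The aim repeats it: the intervention "results in a reduction of a composite endpoint of myocardial infarction, stroke and cardiovascular mortality". Neither limits stroke to one type.

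The only definition is in Endpoint collection and evaluation: "Stroke is defined as characteristic clinical symptoms of stroke accompanied by signs of recent ischemia using an appropriate imaging technique" (CT or MRI). For deaths, the same section says: "Cardiovascular mortality is defined as death due to myocardial infarction, stroke, ruptured abdominal aneurysm, and terminal heart failure"; sudden death is added. An independent committee adjudicates: "The committee will evaluate these events using definitions for the different events which are also used in other Dutch trials". Those trials are cited but their definitions are not reproduced.

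Table 3 (Treatment groups) lists "Acetylsalicylic acid" as standard medication for all patients, and Table 2 sets blood-pressure goals for all. In the intervention arm the nurse practitioner actively pursues "the use of specified cardioprotective medication and the implementation of current guidelines". The physician-care arm receives no extra incentive to follow the guidelines.

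**The concern.** The name of the component and its definition describe different sets of events. The definition has two conditions joined by *and*: clinical symptoms, and imaging signs of recent ischemia. A patient who survives a brain haemorrhage meets the first and fails the second, and no other component of the composite takes that event in.

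The trial could therefore report an effect on stroke when one type was never counted. This matters more here than in many trials because the intervention is meant to raise the use of treatments that could plausibly move haemorrhagic stroke: an antiplatelet drug might add such events and better blood-pressure control might prevent them. Neither effect would register in the primary endpoint, which also drives the interim analyses reviewed every six months.

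**Working it through.** **1. Apply the definitions to each kind of event.**

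| Event | Meets the stroke definition? | Enters the composite another way? |
|---|---|---|
| Non-fatal ischemic stroke, visible on imaging | Yes | Not needed |
| Non-fatal haemorrhagic stroke, visible on imaging | No | No |
| Non-fatal clinical stroke, imaging negative or not done | No | No |
| Fatal haemorrhagic stroke | No | Unclear: stroke death is listed with no imaging condition and no type |

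The clear loss is in the second and third rows.

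**2. Look for a rationale in the same section.** Deaths from ruptured abdominal aneurysm and terminal heart failure count, so the composite is not confined to ischemic events. Myocardial infarction needs ECG changes *or* an enzyme pattern; stroke needs symptoms *and* a positive image. No reason for an ischemia-only stroke component is given.

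**3. Reproduce the plan's own sample size.** Inputs from Power analysis: control risk 13.5%, halved to 6.75%; 80% power; two-sided 5%; 640 patients.
- Pooled two-proportion formula: n per arm = [1.960·√(2 × 0.10125 × 0.89875) + 0.842·√(0.135 × 0.865 + 0.0675 × 0.9325)]² / 0.0675² = 313, or 626 in total. With 320 per arm, power is 80.9%.
- HR = ln(0.9325)/ln(0.865) = 0.482, matching the stated 0.48. The Freedman formula gives 65 events, and 65/0.10125 = 642 patients.

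The stated figure reproduces. Expected events are 640 × 0.10125 = 64.8.

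**4. Events that might go uncounted (shares assumed; none is in the documents).** Let strokes be 25-40% of composite events, 10-20% of strokes be haemorrhagic, and a further 5-15% have no imaged lesion.
- Haemorrhagic only: 0.25 × 0.10 to 0.40 × 0.20 = 2.5-8%, or 1.6-5.2 of 64.8 events.
- Both kinds: 0.25 × 0.15 to 0.40 × 0.35 = 3.75-14%, or 2.4-9.1 events.

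If the 13.5% included all strokes and the halving is kept, two-proportion power with 640 patients is 80.1% at 2% lost, 78.7% at 5%, 77.2% at 8% and 73.6% at 15%.

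Enrolment had reached 793 by 15 December 2005 (Recruitment and screening). Taking off the planned 15% loss gives 793 × 0.85 × 0.10125 = 68.2 events. Removing the worst-case 14% leaves 58.7. With power = Φ(√(events/4) × |ln 0.48| − 1.96), 59 events give about 80%, the design target.

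**5. Effect on the estimated relative risk (assumed).** Add uncounted strokes with 5-year control risk h and relative risk r. The all-stroke relative risk is (0.0675 + h·r)/(0.135 + h).
- h = 0.3%, r = 1: 0.0705/0.138 = 0.51.
- h = 1.0%, r = 2: 0.0875/0.145 = 0.60.
- r = 0.5, any h: 0.50, no distortion.
- h = 1.0%, r = 0.25: 0.070/0.145 = 0.48, so the restricted endpoint would understate benefit.

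**6. Effect on the sequential statistic.** Z is observed minus expected control-arm events. With equal arms, each uncounted nurse-arm event moves Z by +0.5 (toward benefit) and each uncounted control-arm event by −0.5. At about 64 events V ≈ 16, so the SD of Z is about 4 and each event is worth one eighth of an SD.

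**The case against.** **The board would see these events anyway.** It reviews adverse events every six months, safety data are monitored one-sided, and cardiovascular morbidity is a secondary outcome. This stands against a reader who infers that haemorrhagic harm or benefit would be invisible: what is shown is absence from the primary endpoint. Whether the secondary outcome covers haemorrhage is not stated.

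**Fatal haemorrhages may count.** The mortality definition names stroke with no imaging requirement. This stands: exclusion of fatal cases is not shown, only left unclear.

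**The committee's cited definitions may be broader, and an article condenses the full protocol.** Possible, so it cannot be said that these events are lost in practice. But the article does not omit a definition; it prints one. If the cited definitions differ from it, the two need reconciling.

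**Bias toward the nurse arm is not established.** The standard medication applies to both arms, so a difference needs differential uptake, and the authors themselves expect attenuation. The two plausible mechanisms pull in opposite directions. A reader might infer that the definition favours the intervention; the documents do not support a direction.

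**Imaging is a safeguard.** Patients and physicians are not blinded, and nurse-arm patients may be seen more often. Requiring a positive image limits differential ascertainment. This stands against counting clinically diagnosed strokes without imaging in the primary endpoint. It does not argue against counting an imaged haemorrhage.

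**Conclusion.** The mismatch is real on the face of the text: a component called stroke is defined so that non-fatal haemorrhagic stroke does not qualify, and the status of fatal haemorrhage is left open. This is a stated rule that miscounts against its own label, not a detail left to another document.

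Its size is not known. The event losses and relative risks worked out above rest on assumed shares and show only plausible orders of magnitude: a few events, with a shift in the estimate that may go either way or be nil. A reader might infer that the trial is underpowered. That does not follow: the sample size reproduces, the documents do not say whether the 13.5% includes haemorrhagic strokes, and enrolment above the minimum keeps power near 80% even in the worst case assumed.

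Severity: should be fixed, because the conclusion about stroke depends on it and the correction is cheap.

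**What to change.** Before outcome results by arm are seen outside the monitoring board:

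1. Amend the definition so that stroke means characteristic clinical symptoms with imaging evidence of recent ischemia *or* haemorrhage.
2. State that death due to stroke includes both types.
3. Report ischemic and haemorrhagic strokes separately by arm, to the monitoring board and in the results.
4. Put clinically diagnosed strokes with negative or no imaging in a prespecified sensitivity analysis, outside the primary count.

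If the component is meant to be ischemic only, keep the definition, call it imaging-confirmed ischemic stroke in the aim, abstract and conclusions, and report haemorrhagic stroke by arm as a separate outcome. State in that case too how fatal haemorrhage is classified.

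Cost: one endpoint amendment, a line in the committee's rules, and a re-check of already adjudicated dossiers blinded to allocation. Widening the definition lets in a few events less specific to atherothrombosis, and it changes a primary endpoint after recruitment began, so the date and reason should be recorded. No treatment changes.
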